#### Secondary endpoint

2.10.2

HAMA Score and SCL-90 Score will be assessed as secondary outcomes. HAMA Score is an essential diagnostic tool for anxiety disorders and is commonly used in clinical diagnosis and classification of anxiety disorders. SCL-90 Score has advantages of large capacity, rich symptoms, and more accurate characterization of patient's conscious symptoms. It can show mental status of the interviewee which is closely related to the quality of life. They will be tested at week 0, week 4, week 8 and week 12, and during the follow-up period.

#### fMRI and 1H-MRS

2.10.3

fMRI will focus on the activity of the amygdaloid nucleus and the connection between the fear center and fear network to reflect the changes of the brain's function of perimenopausal PD patients before and after treatment. 1H-MRS will test the Glutamate-GABA level of these brain tissues to explore the relations between neural activity and amino acid metabolism. Differences in imaging changes will be compelling evidence.

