**Methods::**

The parallel designed, exploratory randomized controlled trial will include 70 outpatients with perimenopausal PD recruited from two hospitals of Chinese Medicine. These subjects will be randomly allocated to an intervention group (Group Embedding) and a control group (Group Medication) in a 1:1 ratio. The subjects in the intervention group will receive acupoint catgut embedding treatment two weeks a time in the following predefined acupuncture points: Shenshu (BL23), Sanyinjiao (SP6), Guanyuan (RN4), Ganshu (BL18), Zusanli (ST36) and Pishu (BL20). The included women of the control group will take 0.4 mg Alprazolam tablet orally, 1 tablet a time, 3 times a day. There is a study period of 3 months and a follow-up period of 1 month for each group. The primary outcomes will be the following therapeutic indexes: the frequency of panic attack, Panic Disorder Severity Score (PDSS), and Panic-associated Symptoms Score (PASS) during the observation period and follow-up period. The changes in Hamilton Anxiety Scale (HAMA) Score and Symptom Checklist 90 (SCL-90) Score will also be compared between these two groups. Additionally, functional magnetic resonance imaging (fMRI) and proton magnetic resonance spectroscopy (1H-MRS) scans will be done before and after the observation period to show cranial neuroimaging changes.

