### Intervention

2.9

At the screening visit, participants will sign the informed consent form. In a baseline questionnaire, information will be obtained age, occupation (physical/non-physical), education level, last menstrual period, previous use of acupuncture and expectation to acupoint catgut embedding therapy. Moreover, Panic Disorder Severity Score (PDSS), Panic-associated Symptoms Score (PASS), Hamilton Anxiety Scale (HAMA), Symptom Checklist 90 (SCL-90) must be completed at the baseline (week 0). The frequency of panic attack will also be recorded. Thereafter, study subjects will be randomized. There is a 3-months study period and a 1-month follow-up period for each group. In the study period, the frequency of panic attack, PDSS, PASS, HAMA Score and SCL-90 Score will be evaluated every 4 weeks. fMRI and 1H-MRS will be tested two times: in week 0 and week 12. A detailed process flow according to the SPIRIT figure can be seen in Table 1.

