#### Intervention group

2.9.1

Acupoint catgut embedding therapy will be applied to patients in the intervention group fortnightly, a total of 6 times during 3 months. Main acupoints are BL23, SP6 and RN4. If it is a liver-kidney yin deficiency case, BL18 will be added. If it is a kidney yang deficiency case, ST36 and BL20 will be included. In each treatment, RN4 is a required acupoint. The rest acupoints can be used in the alternation of left/right side. The location method is according to *Location of Acupoints* the National Standards of P.R promulgated by the State Bureau of Technology Supervision. The operating method follows the National Standards of P.R (GB/T 21709.10-2008) manipulations of acupuncture and moxibustion—Part 10 Acupoint catgut embedding. Details about the intervention group interventions are described in the Standards for Reporting Interventions in Clinical Trials of Acupuncture (STRICTA) checklist in Table 2.^[14]^

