#### Control group

2.9.2

In the 3-months study period, patients in the control group will take Alprazolam tablet (Guangxi Southpearl Pharmaceutical Co., Ltd.) with the size of 0.4 mg orally, 1 tablet a time, 3 times a day.

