#### fMR examination procedure

2.9.3

The fMRI (PRISMA 3.0T Magnetic Resonance Imaging Scan; Siemens Company) examination will be performed to collect brain images offering more visualized proof. During the scanning procedure, subjects will be asked to keep quiet and their eyes closed. In the meantime, they need to empty their minds but avoid sleeping. The researcher will check whether the participants are awake during the process. For T1-weighted images (Spin Echo) scan, parameters are TR/TE = 2100 ms/24 ms, field of view = 240 mm × 240 mm, matrix size = 256mm × 256 mm, voxel size = 3 × 3 × 3mm^3^, 18 sections, 5 mm thickness, 1.5 mm slice gap, 20.83 Hz/pixel bandwidth. DTI images (SE EPI), in transaxial plane aligned to the anterior and posterior commissure line, are acquired with the following parameters: matrix size = 128mm × 28 mm, field of view = 240mm × 240 mm, 3.8 mm slice thickness, 28 slices centered on the corpus callosum, b-value = 1000 s/mm^2^. The parameters of T2-weighted images (Gradient-Echo, Echo Planar imaging, GRE-EPI) are TR/TE/FA = 3000ms/60ms/90°, field of view = 240mm × 240 mm, matrix size = 64mm × 64 mm, 18 sections, 5 mm thickness. The data acquisition is carried out 12 seconds after the start of scanning, and the scanning time is 5 minutes and 12 seconds. The blood oxygen level dependent (BOLD) signal imaging sequence is monitored by RTIP.

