### Adverse events

2.12

In research, some adverse reactions may occur.

1.There are a few common responses after the acupoint catgut embedding:Local reactions: Mostly some sterile inflammations with inflamed hot pain occur within 5 days. Some cases may be more severe, like a small amount of milky-white exudation at the embedding spot caused by fat liquefaction because of suture stimulation. Circumstances above should not require any special treatment.General reactions: Some patients may experience temperature rising after treatment 4 to 24 hours, mostly around 38. It will fade away in 2 to 4 days by itself. Usually, hemogram of each patient may rise in different levels, and it will return to normal in 3 to 5 days.2.There are a few adverse responses after the acupoint catgut embedding:Pain: Apply hot compress if there is pain at embedding acupoint.Secondary infections: Lack of strict asepsis and inappropriate protection for the wound could cause secondary infection, which mostly brings about some inflammatory symptoms like local swelling, progressive pain, and fever in 3 to 4 days after the implantation. Hot compress and anti-infective treatment would be helpful.Nerve injuries: It is usually caused by an incorrect operation or excessive stimulation or carelessness, and can be avoided with careful operation.Hemorrhage: It is usually caused by a puncture on the vessels or excessive stimulation. Pressure put on the puncture point would stop the bleeding.Suture allergies: Local itching or swelling or fever can be remitted by antianaphylaxis treatment.3.Alprazolam is one of the Benzodiazepines. Its principal effects are anti-anxiety and antidepressant. Common adverse reactions are as following:Somnolence, vertigo, and weakness, etc. The large dose may cause dystaxia, tremor, uroschesis or jaundice.Addiction. Drug withdrawal may cause withdrawal symptoms after being used for a long period, showing as emotional or melancholy.A few patients may suffer dry mouth, inattention, hyperhidrosis, palpitation, constipation or diarrhea, blurred vision, and hypotension.

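### The week-12 scan probably catches control patients on alprazolam, so a between-arm imaging difference cannot be attributed to embedding's neural mechanism

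*Protocol article*

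**What the plan says.** - **Aim.** The Abstract (Background) and the Introduction set out to explore the neural mechanism of embedding. The Abstract also plans to correlate brain activation, amino acids and clinical outcomes.
- **Scans.** Section 2.9: "fMRI and 1H-MRS will be tested two times: in week 0 and week 12". The Abstract (Methods) puts it as "scans will be done before and after the observation period to show cranial neuroimaging changes". The clinical scales are repeated in the follow-up month (sections 2.10.1 and 2.10.2); no follow-up scan is described.
- **Control drug.** Section 2.9.2: "In the 3-months study period, patients in the control group will take Alprazolam tablet", three times a day. No drug-free interval before the scan is described. Section 2.12 classes alprazolam as a benzodiazepine and lists as common reactions "Somnolence, vertigo, and weakness, etc".
- **Embedding.** Section 2.9.1: "fortnightly, a total of 6 times during 3 months".
- **Scan conditions.** Section 2.9.3 has subjects lie quietly with eyes closed; "they need to empty their minds but avoid sleeping". A researcher checks that they are awake.
- **Targets and inference.** Section 2.10.3 names amygdala activity, the fear network and the Glutamate-GABA level, and ends: "Differences in imaging changes will be compelling evidence". The Discussion treats a return of amygdala activity towards normal as a companion of clinical improvement.

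**The concern.** The comparator is a sedating, anxiety-reducing drug, and the single post-baseline scan falls in the period when it is taken. Subtracting the week-0 scan does not remove the drug state, because allocated alprazolam starts only after baseline. A between-arm difference in imaging change therefore has at least three possible sources: an effect of embedding on the brain, the state of a control patient's brain on the drug that day, and different degrees of recovery. The protocol has no means of separating them.

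At stake is the mechanism conclusion. A difference could appear although both arms recovered equally, or a drug effect in the same direction could hide an effect of embedding. The primary and secondary clinical comparisons are not affected.

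**Working it through.** **1. Timing.** Inputs are the week-12 scan and the two treatment periods in section 2.9 ("There is a 3-months study period and a 1-month follow-up period for each group").
- Week 12: 12 × 7 = 84 days.
- Three calendar months: 365.25 / 4 = 91.3 days.
- Six fortnightly embedding sessions: 6 × 14 = 84 days.

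The scan thus falls at or shortly before the end of alprazolam dosing, and at the end of the embedding course. Scans per patient after baseline: 1. Scans in follow-up: 0.

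**2. What the between-arm difference contains.**

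| Component at week 12 | Embedding | Medication |
|---|---|---|
| Symptom recovery since week 0 | yes | yes |
| Direct effect of embedding | possible | no |
| Current alprazolam state | no (not allocated) | probable |

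Randomisation makes the difference a fair estimate of strategy against strategy. It does not say which row produced it.

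**3. Pooled correlations.** If change in amygdala or Glutamate-GABA measures is correlated with change in the Panic Disorder Severity Score (PDSS) over all 70 patients, a drug-induced shift in one arm enters the correlation through the difference in arm means. Computing it within each arm removes that part.

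**4. Size, as an illustration.** The protocol gives no figure for alprazolam's effect on any imaging measure, nor its direction, so a range is assumed: 0.3 to 0.5 SD of the change measure, with equal recovery and no embedding effect. Two-sided two-sample t test at 0.05, noncentrality = d × √(n/2):

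| n per arm | d | Noncentrality | P ≤ 0.05 expected in |
|---|---|---|---|
| 35 | 0.3 | 0.3 × √17.5 = 1.25 | about 24% |
| 35 | 0.5 | 0.5 × √17.5 = 2.09 | about 54% |
| 28 | 0.3 | 0.3 × √14 = 1.12 | about 20% |
| 28 | 0.5 | 0.5 × √14 = 1.87 | about 45% |

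The 28 comes from the 20% maximum loss in section 2.13: 35 × 0.8 = 28. With no drug effect the figure would be 5%.

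The protocol has no sample-size figure for imaging to reproduce; its calculation in section 2.13 rests on the Kuppermann index and plays no part here.

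**The case against.** The case on the other side has several good parts.

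- **The challenged sentence is not explicit.** Section 2.10.3 speaks of change before and after treatment and names neither a between-arm contrast nor embedding; section 2.1 speaks of the mechanism of the disease. This stands. The between-arm reading comes from combining the sentence with the aims in the Abstract and Introduction and with section 2.14, which tests all curative-effect indexes within and among groups. A sentence that can be read either way still needs rewording.
- **Being on the drug at the scan is an inference.** The Abstract places the second scan after the observation period, the interval from last tablet to scan is not given, and Table 1 could not be read in the available copy. Hence *probably*. If dosing had just stopped, section 2.12 warns of withdrawal symptoms after long use, so the scan still need not show recovery alone.
- **Wakefulness is checked.** This guards against sleep, but not against drowsiness short of sleep or a direct drug effect.
- **Both arms are scanned at the end of active treatment.** True, and the Discussion describes embedding as continuing stimulation. Only one arm is allocated a sedating drug, though.
- **The trial calls itself exploratory, and imaging is neither a primary nor a secondary endpoint.** True; this limits the damage, but it is also why the stronger wording does not fit.

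A reader might infer that the mechanism conclusion would be wrong whichever way the imaging falls, or that alprazolam is known to quiet the amygdala or shift the Glutamate-GABA signal. The documents support neither. They describe the drug's class, its anti-anxiety and antidepressant effects and its common reactions, and nothing about its effect on these measures. The result would be unattributable, not necessarily wrong.

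**Conclusion.** The point holds as a limit on inference. The between-arm difference in imaging change validly compares the two strategies at week 12. It cannot be attributed to embedding's neural mechanism, because it mixes the controls' probable drug state with recovery. Pooled imaging-clinical correlations share the problem.

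It concerns every control patient scanned on treatment at week 12: up to 35, or about 28 after the allowed loss. The conclusion rests on the stated schedule, with no drug-free interval described. The 20% to 54% range rests wholly on the assumed drug effect and equal recovery, and shows only that a misleading difference could be common. The change is worth making because it alters what the trial can claim on a headline aim, at little cost.

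**What to change.** 1. **Section 2.10.3.** Replace the closing sentence by a statement that the imaging is exploratory, that the between-arm contrast compares embedding with the probable on-alprazolam state, and that it will not by itself be used to infer embedding's mechanism.
2. **Correlations.** Run the imaging-clinical correlations already announced in the Abstract separately within each arm, for example change in amygdala and Glutamate-GABA measures against change in PDSS. Report them as exploratory: with no sham or untreated arm, a within-arm association cannot separate embedding from natural course, expectation or regression to the mean.
3. **Scan form, week 12.** Record time since the last alprazolam tablet (control arm) and a sleepiness rating (both arms). Use them for description and for a check within the control arm. They should not be covariates in the between-arm contrast: time since last tablet is undefined under embedding, and sleepiness is measured after randomisation and may be an effect of treatment, so adjusting for it can bias the comparison.
4. **Timing.** Reconcile the wording of the Abstract, section 2.9 and section 2.9.2 so that it is clear how the second scan lies relative to the alprazolam period.

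**Cost:** some rewording and two items on the scan form; no extra scan and no change to treatment. The price is a weaker, correlational mechanism claim from at most about 35 patients per arm, about 28 after the allowed loss.

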### Safety assessment

2.11

At every visit, physical examination will be performed, and adverse events will be checked. Blood samples will be collected at week 0 and week 12. Blood routine test, liver function (Alanine aminotransferase) and kidney function (serum creatinine) will be done at the beginning and the end of the intervention period.

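### Adverse events are checked at every visit, and the visible text gives the embedding arm more contacts than the alprazolam arm, so recording of mild or short-lived events may differ between arms

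*Protocol article*

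**What the plan says.** Section 2.11 (Safety assessment) sets one rule for collecting adverse events, worded the same for both arms: "At every visit, physical examination will be performed, and adverse events will be checked". It does not define a visit or state a recall period.

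The contacts stated elsewhere in the protocol article are:

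- **Embedding arm** (2.9.1): "Acupoint catgut embedding therapy will be applied to patients in the intervention group fortnightly, a total of 6 times during 3 months".
- **Alprazolam arm** (2.9.2): tablets taken "orally, 1 tablet a time, 3 times a day" over the 3-month study period. No clinic attendance or dispensing interval is given.
- **Both arms** (2.9): "the frequency of panic attack, PDSS, PASS, HAMA Score and SCL-90 Score will be evaluated every 4 weeks". Section 2.10.2 gives the weeks: "They will be tested at week 0, week 4, week 8 and week 12, and during the follow-up period".

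Blood tests for safety are at weeks 0 and 12 in both arms (2.11). Section 2.1 names safety as an aim alongside effectiveness. Section 2.8 leaves patients and treating staff unblinded, with outcome measurers and statisticians blinded. Table 1 holds the schedule of interventions and assessments, but its content is not shown.

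**The concern.** A rule tied to visits observes both arms equally only if the arms have the same visits. Here one treatment requires attendance every two weeks, and the other is taken as tablets with no attendance stated. Read literally, the rule gives one arm more occasions to report an event than the other.

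This goes beyond missing detail: the stated rule and the stated schedules together produce the imbalance. An analysis plan cannot recover an event that nobody asked about, so the remedy belongs in data collection, in section 2.11.

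At stake is how the two arms' adverse-event counts are read. The Discussion sets the side effects of existing treatments against a therapy said to have none, so readers will compare the arms on this. More frequent checking would tend to raise the embedding counts. It could hide a real tolerability advantage of embedding or create an apparent disadvantage.

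**Working it through.** **Inputs.** Embedding sessions every 2 weeks, 6 in all (2.9.1). Shared assessments at weeks 0, 4, 8 and 12 and in follow-up (2.9, 2.10.1, 2.10.2). A study period of 3 months, taken as 12 weeks because the last study-period assessment is at week 12.

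**Assumptions.** Each session counts as a visit. A session and an assessment due in the same week are one visit. Follow-up has one visit, at about week 16. The alprazolam arm attends only the shared assessments.

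**Step 1: the plan's own figure.** 12 weeks / 2 weeks = 6 sessions, which agrees with 2.9.1.

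**Step 2: contacts per arm.** The embedding arm's visits are the session weeks combined with the assessment weeks. Sessions at weeks 0, 2, ..., 10 or at weeks 2, 4, ..., 12 give the same combined set.

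| Period | Embedding | Alprazolam | Ratio |
|---|---|---|---|
| Post-baseline, treatment period | 2, 4, 6, 8, 10, 12 = 6 | 4, 8, 12 = 3 | 6/3 = 2.0 |
| Post-baseline with follow-up | 7 | 4 | 7/4 = 1.75 |
| All visits with baseline | 8 | 5 | 8/5 = 1.6 |

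**Step 3: sensitivity to the assumptions.** If sessions were always held apart from assessments, the treatment period would have 6 + 3 = 9 visits against 3, a ratio of 3.0. If the alprazolam arm also came fortnightly, or if visit meant only the shared assessments, the ratio would be 1.0.

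**Step 4: what unequal contacts could do to recording.** The documents give no recall period, so this step is an illustration over a range. Suppose an event falls at a random time in the treatment period and is reported only if it lies within w days before a check. The chance of recording is min(1, w/14) with fortnightly checks and min(1, w/28) with 4-weekly checks.

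| w (days, assumed) | Embedding | Alprazolam | Ratio |
|---|---|---|---|
| 3 | 3/14 = 21% | 3/28 = 11% | 2.0 |
| 7 | 7/14 = 50% | 7/28 = 25% | 2.0 |
| 14 | 100% | 14/28 = 50% | 2.0 |
| 28 | 100% | 100% | 1.0 |

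The effect therefore runs from a doubling to nothing, depending on how far back patients report. Events that persist until the next check, or that are too serious to forget, behave like the last row.

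**Step 5: with a common schedule.** Checks at weeks 4, 8, 12 and follow-up in both arms give 4 against 4, a ratio of 1.0.

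**The case against.** The strongest objection is that the visit schedule is in Table 1, which cannot be seen. A journal article may also leave the adverse-event form, recall period and dispensing contacts to the full protocol. Section 2.9.2 gives no visit interval, so the ratio comes from setting embedding sessions against the shared assessments, not from the alprazolam dosing. Section 2.15 mentions checks of medicine use without saying when, and those could be further contacts. All of this stands, and it makes the point conditional. It does not remove it, because nothing in the visible text equalises the contacts.

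A reader might infer more than the documents support:

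- **That the two arms' adverse-event rates cannot be compared.** If each check covers everything since the last one, both arms are observed for the same time. Only forgotten, mild or brief events can differ.
- **That control patients must recall 28 days.** Section 2.11 states no recall period.
- **That a planned test of adverse events is biased.** Section 2.14 lists chi-square and Fisher tests for count data in general. It does not assign them to adverse events.
- **That the gap can be sized by giving every check the same chance of detection.** With an assumed 0.3 per check, six checks give 1 − 0.7^6 = 88% and three give 1 − 0.7^3 = 66%. This treats a 28-day check as no better than a 14-day one, which assumes the bias. If a 28-day check covers two 14-day periods, its chance is 1 − 0.7^2 = 0.51, and three checks give 1 − 0.49^3 = 88%, with no gap.
- **That alprazolam effects are the transient ones.** Section 2.12 does not call them so. The reactions it describes as brief are mainly those of embedding, such as a fever that passes in 2 to 4 days.

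The objection also holds against one possible remedy. Comparing the arms only at shared weeks, with session-only events moved aside, could drop procedure reactions from the comparison and favour embedding.

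**Conclusion.** The point holds in a limited form. On the visible text, the every-visit rule gives the embedding arm 6 post-baseline checks against 3 in the treatment period, and 7 against 4 with follow-up. Recording of mild or short-lived events may therefore differ between arms, in a trial with open treatment and safety among its aims. The likely direction is higher embedding counts relative to control, so the imbalance is unlikely to give embedding a false safety advantage.

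The size of any effect on counts cannot be derived from the documents. Under the assumed recall windows it ranges from a ratio of 2.0 to none. Serious or persistent events and the week 0 and week 12 laboratory tests are little affected.

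The conclusion rests on three assumptions: that treatment sessions count as visits, that the alprazolam arm has no contacts beyond the shared assessments, and that follow-up has one visit. If Table 1 equalises contacts, or if visit means only the shared assessments, the point falls away.

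**What to change.** In section 2.11:

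1. Ask one standard adverse-event question in both arms at weeks 4, 8, 12 and follow-up, covering the whole period since the last shared assessment. Base the between-arm comparison of adverse events on the answers.
2. Flag on the case report form the visit at which each event was recorded.
3. Also report all events by arm, including those recorded only at embedding sessions, so that no procedure reaction drops out of the safety report.
4. State whether a treatment session counts as a visit. If Table 1 already gives the arms equal contacts, say so in the text; no further change is then needed.

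The cost is some wording, one flag on the case report form and a second tabulation. No visit is added.
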